## Exploratory objectives

1. To investigate the effect of celgosivir on the immunological profile of dengue fever patients

Hypothesis: The maximal change from baseline between Day 2 and 5 will be lower for patients taking celgosivir than for those taking placebo for the following cytokines: (a) TNF- (b) IL-6, (c) IL-12, (d) interferon-, (e) IP-10 and (f) MCP-1.

1. To investigate the effect of celgosivir on the use of analgesic medications of dengue fever patients

Hypothesis: Patients taking celgosivir will use less analgesic medications from Day 1 to Day 5 than those taking placebo.

1. To investigate the effect of celgosivir on the intensity of joint and muscle pain of dengue fever patients

Hypothesis: Patients taking celgosivir will experience a lower intensity of joint and muscle pain from Day 2 to Day 5 than those taking placebo.

# Study Design

## Summary

This is a randomized, double blind, placebo-controlled, Phase 1b clinical study of celgosivir in adults age 21 to 60 with fever 38C of 48 hr duration, who meet at least two criteria indicating probable dengue infection, and who test positive for dengue infection by a point of care NS1 strip assay. Patients meeting all inclusion and exclusion criteria will be enrolled and admitted to the Investigational Medicine Unit (IMU).

Table 1 Study Design

| Cohort | N | Dose | Key Inclusion Criteria | Primary Outcome | Secondary Outcomes | Exploratory Outcomes |
| --- | --- | --- | --- | --- | --- | --- |
| 1 | 25 | Placebo | • Fever ≥38°C of ≤48 hr duration | • Viremia (laboratory) | • Safety & tolerability & PK |  |
| • Time to viral clearance | • Immuno-profiling |
| • positive NS1 strip assay | • NS1 | • Usage of analgesics |
| 2 | 25 | 400 mg loading dose then 200 mg q12hr | • 2 symptoms of probable dengue infection | • Fever (clinical) | • Leukocyte & Platelet count, Hemocon-centration | • Duration & magnitude of symptoms |
|

Fifty (50) patients will be randomized 1:1 to celgosivir or placebo. Capsules of placebo or celgosivir will be administered for 5 days. Patients will be given an initial loading dose of 400 mg followed by a maintenance dose of 200 mg every 12 hr for a total of nine (9) doses. Drug should be taken 1 hr before consuming food or 2 hr afterwards. Patients will be placed on a special diet of protein, vitamins, and glucose containing minimal complex sugars or starches. Oral intake of fluids will be recorded. While in hospital from Day 1 to Day 5, daily clinical exams will be conducted, and blood samples will be collected for plasma viral load, NS1, hematology, clinical chemistry, cytokine levels and safety observations. During this period, eight serum samples will be obtained for drug levels. On Study Day 5, after blood draws, administration of the last dose, safety assessments, determination of risk for DHF or DSS, and satisfactory clinical status, the patient will be discharged. Patients at risk for or who have dengue hemorrhagic fever (DHF) or dengue shock syndrome (DSS) will remain in hospital until fit for discharge. Patients who progress to DHF or DSS may require intravenous fluids, platelet and/or blood transfusions and evaluations from other clinical specialists. At discharge, the patient will be asked to return on Study Days 7, 10, and 15 for blood sampling and safety assessments. Patients will complete visual analog scales for joint and muscle pain (VASP), and be evaluated for safety and tolerability daily while in hospital and at each subsequent outpatient visit. While in hospital, concomitant usage of analgesics will be recorded. As an outpatient, patients will keep a diary of concomitant usage of analgesics. If the patient remains in hospital past day 5, planned outpatient study assessments will be collected in hospital.

The patient will complete the study on Study Day 15 after the investigator has completed the final assessment, unless ongoing adverse events require monitoring. For subjects prematurely terminating participation in the study, assessments planned for Study Day 15 will be obtained if possible, and study completion evaluations must be performed.

Serum or plasma samples for viremia, quantitative NS1, immunological profile, DNA and RNA analysis, and PK will be transferred to Duke-NUS, Singapore Immunology Network, National University of Singapore or other laboratories for analysis and/or storage. The period of storage will not exceed 5 years.

After all study assessments have been completed on all patients and the database is locked, unblinding will occur. The primary virological endpoint will be the mean of virological log reduction (VLR) Study Day 2 to 4 between placebo and study drug groups. The primary clinical endpoint will be a reduction in fever AUC above baseline. Secondary endpoints for antiviral activity will be time to viral clearance, serum NS1 levels, leukocyte and platelet count, and hemoconcentration.

Secondary endpoints for assessing safety and tolerability are the number and severity of all adverse events and severe adverse events related to study drug compared to placebo using the 2009 WHO classification for grading adverse drug events. In addition, eight (8) samples for celgosivir serum concentrations will be obtained for population PK analysis.

Exploratory endpoints will be concentrations of various cytokines between placebo and treated groups, and changes in RNA expression of immunomodulatory genes. The trial will also assess the validity of the VASP and concomitant usage of analgesics between placebo and treatment groups as other measures of drug activity.

## Selection and Withdrawal of Patients

### Inclusion Criteria

1. Male or female, age 21-65 years
2. Fever of  38C (directly measured or patient reported) of  48 hr duration.
3. At least two of the following criteria indicating probable dengue infection:
   1. Live or work in or recent travel to dengue endemic area
   2. Nausea and vomiting
   3. Presence of rash
   4. Aches and pains, including headache, or retro-orbital, muscle or joint pain
4. Positive NS1 strip assay or PCR
5. Able and willing to give written or oral informed consent
6. Willing to be an inpatient for from Study Day 1 to 5, and to return to the IMU on Study Days 7, 10, and 15.
7. Willing to keep a diary of pain medication usage and side effects

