# Study Procedures

## Methods and Assessments

Patients who present at the polyclinics, Tan Tock Seng Hospital, at the Emergency Departments (ED), SGH and NUH, at general practitioner’s office, or are self-referred, male or female, age 21 to 60, who have fever  38C of  48 hr duration, at least two criteria indicating probable dengue infection, and a positive NS1 strip assay will be referred to the Investigational Medicine Unit (IMU) to undergo screening. Eligible patients will be approached and invited for participation. The patient will be given the patient information sheet and allowed to ask any questions about the trial. The Principal Investigator or a Co-investigator will take informed consent. Patients meeting all inclusion and exclusion criteria and who agree to participate will be enrolled and admitted to the Investigational Medicine Unit (IMU).

A flowchart showing the patients’ activities throughout the whole study is shown in . A table summarizing the assessment schedule for the study is shown in the Appendix, Table 2.

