Viral clearance is indicated by an “undetectable” lab test results in the Dengue PCR at baseline, Day 2, Day 3, Day 4, Day 5 and Day 7. The time from baseline to viral clearance will be analyzed using a Kaplan-Meier analysis.

Serum NS 1 is measured by lab test results of “Dengue Non-structure protein 1”. The mean serum NS 1 between day 2 and Day 5 inclusive will be computed for each patient, and compared between the two groups using linear regression, adjusting for primary vs secondary infection. NS1 clearance is indicated by an undetectable lab test result in the NS1 assay. The time to NS1 clearance will be analyzed using a Kaplan-Meier analysis and compared using log rank test.

Leukocyte is measured by lab test results of “Urinalysis”, while platelet count is measure by the lab test results of “Hematology”. Both outcomes will be measured at baseline, Day 2, Day 3, Day 4 and Day 5. The maximum changes from baseline in leukocyte and platelet counts between Day 2 and Day 5 will be computed for each patient, and compared between the two groups using a two-sample t-test.

Hemoconcentration is defined as the hemaocrit at each day compared to that at Day 15. If the reference value at Day 15 is not available, use the value at Day 10. If both values at Day 10 and Day 15 are not available, the patient will be treated as a missing case. The mean maximal hemoconcentration from Day 2 to Day 5 will be computed for each patient, and compared between the two groups using a two-sample t-test.

Clearance celgosivir and volume of distribution of celgosivir will be obtained from concentration-time date by standard PK analysis. The correlation of these PK parameters with weight, age, and sex will be examined by nonlinear mixed effects modeling.

Exploratory outcomes

The various cytokines including TNF-, IL-6, IL-12, interferon-, and MCP-1, are measured by lab test results of “Cytokines” at Study Days 1, 2, 3, 4, 5, 7, 10, and 15. The maximal change from baseline (Day 1) in these cytokines between Day 2 and 15 will be computed for each patient, and compared between the two groups using two-sample t-test.

To investigate whether patients taking celgosivir will use less analgesic medications during the study, analgesic medications recorded during the in-hospital stay and the out-patient diary will between totaled. The total will be compared between the two groups using Fisher exact test.

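### The age limit and entry test are each stated two ways; separately, the viral clearance definition lets an undetectable baseline PCR count as an event at time 0.

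*Protocol*

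**What the plan says.** **Age.** Inclusion criterion 1 in section 3.2.1 reads "Male or female, age 21-65 years". The Summary in section 3.1 describes a "clinical study of celgosivir in adults age 21 to 60 with fever", and section 5.1, which governs referral for screening, says "male or female, age 21 to 60".

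**Entry test.** Inclusion criterion 4 in section 3.2.1 reads "Positive NS1 strip assay or PCR". Section 3.1 describes patients "who test positive for dengue infection by a point of care NS1 strip assay". In section 5.1, patients with "a positive NS1 strip assay will be referred to the Investigational Medicine Unit (IMU) to undergo screening". Table 1 and the Figure 2 flowchart also name the NS1 strip alone. The assessment schedule (Table 2) has a screening row for the strip and no row for an eligibility PCR; viremia is sampled before the first dose as a baseline assessment.

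**Clearance.** Section 6.2 defines viral clearance by undetectable "lab test results in the Dengue PCR at baseline, Day 2, Day 3", and the list continues to Days 4, 5 and 7. Time runs from baseline and is analysed by Kaplan-Meier. For the other marker, "NS1 clearance is indicated by an undetectable lab test result in the NS1 assay"; that sentence names no times. The efficacy set in section 6.2 is everyone who consented and received an enrolment number. Nothing requires detectable virus or NS1 at baseline for either clearance analysis.

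**The concern.** These are two separate problems.

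The first concerns who may enter. Section 5.1 decides who is sent to the unit and section 3.2.1 decides who may be enrolled, and they differ on two criteria. For a patient aged 61 to 65, or one confirmed by PCR alone, site staff and monitors cannot tell from the protocol whether enrolment is correct or a violation. Eligibility is protocol content, so a statistical analysis plan cannot settle it.

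The second concerns what counts as clearance. An NS1 strip can be positive in a patient whose baseline PCR is undetectable. Because baseline is itself a listed clearance time and also the time origin, that patient has an event at time 0. The sample is drawn before the first dose, so the event carries no information about celgosivir, yet it enters the curve of whichever arm the patient joins. With 25 patients per arm, each such patient moves that curve by 1/25 = 4 percentage points.

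**Working it through.** The protocol gives no rate of patients who are positive on one test and undetectable on the other, so it has no figure of its own to reproduce here. The sample size calculation in section 6.1 is not at issue.

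**Step 1: eligibility, side by side.**

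| Place | Age | Entry test |
|---|---|---|
| 3.2.1, criteria 1 and 4 | 21-65 | NS1 strip or PCR |
| 3.1 Summary | 21-60 | NS1 strip |
| Table 1 | not stated | NS1 strip |
| 5.1 referral | 21-60 | NS1 strip |
| Figure 2 | not stated | NS1 strip |

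On both criteria the referral text is narrower than 3.2.1. Anyone who satisfies 5.1 also satisfies 3.2.1 on age and test. The conflict is therefore confined to two groups: patients aged 61 to 65, and patients positive by PCR only.

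**Step 2: which entry rule produces a time-0 viral clearance event?**

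- Strip only: an NS1-positive, PCR-undetectable patient can be enrolled.
- Strip or PCR: the same patient can be enrolled. The extra patients admitted are PCR-positive, so they should be detectable for viral clearance.

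The viral clearance problem exists under both rules, and reconciling eligibility does not remove it.

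**Step 3: NS1 clearance.** A PCR-positive, strip-negative patient can enter only if the PCR route is kept. Such a patient might have undetectable quantitative NS1 at baseline. This is an inference: the quantitative assay is separate from the strip, and the NS1 sentence does not list baseline as a clearance time.

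**Step 4: size, on assumed inputs.** Let f be the share of enrolled patients with undetectable baseline PCR. Assume 4% to 12%.

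- Patients affected: 0.04 × 50 = 2 to 0.12 × 50 = 6.
- Dilution: ignoring censoring, and with the same f in both arms, the proportion not yet cleared at any time is (1 − f) times that among patients detectable at baseline. A between-arm difference D becomes (1 − f) × D, which is 0.96D at 4% and 0.88D at 12%.
- Chance imbalance: a 3 versus 0 split would raise one arm's clearance curve by 3/25 = 12 percentage points at time 0. If exactly three such patients were enrolled and 50 patients were split at random into 25 and 25, the probability that all three fall in the same arm, either one, is (24/49) × (23/48) = 552/2352 = 0.235. Permuted blocks would change this slightly. The expected difference between arms is zero, because section 5.1 places baseline sampling before randomization.

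**The case against.** Both section 3.1 and section 5.1 say that patients must meet all inclusion and exclusion criteria, and the full list is in 3.2.1. A reader could treat 3.2.1 as governing, the Summary as shorthand and 5.1 as a referral filter. That has weight. A reader might infer from the discrepancy that the whole study population is undefined; the documents do not support that, since only the two groups in Step 1 are affected. But 5.1 is operative text and no order of precedence is stated, so the contradiction stands.

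On clearance, the listed times match the viremia sampling schedule in Table 2, so baseline may have been meant as a sampling time rather than an event time. Rules for undetectable values are also ordinary content for a statistical analysis plan, and one is promised before unblinding. This narrows the point, but the protocol sentence, followed as written, still admits the event. That is wording fixed badly, not detail left for later.

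Three stronger readings go too far:

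- That both clearance endpoints contain events before dosing. Viral clearance could, on the literal text. For NS1 clearance it is only possible, for the reasons in Step 3.
- That the treatment comparison is biased. Baseline status precedes randomization, so any imbalance is chance.
- That the primary virological log reduction becomes uninterpretable. A patient undetectable at baseline has no measurable reduction, but handling values below the detection limit belongs in the statistical analysis plan and is not counted as a fault here.

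**Conclusion.** The eligibility contradiction is certain from the current text and should be corrected. Its reach is limited to patients aged 61 to 65 and patients positive by PCR only. Which version is right is for the sponsor.

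The viral clearance wording is a separate, smaller defect that does not depend on the entry test finally chosen. Its effect on this secondary endpoint is some dilution and a possible chance imbalance. The figures of 2 to 6 patients, 0.88D to 0.96D and 12 percentage points rest on an assumed share or an assumed split; the documents support no particular value, and the true number could be zero. The extension to NS1 clearance is precautionary and matters mainly if PCR-only entry is retained.

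**What to change.** 1. State one age limit and one entry test, identically, in sections 3.1, 3.2.1 and 5.1, and carry the entry test through Table 1 and Figure 2. If PCR remains an entry route, show it as a screening test in Table 2.
2. In section 6.2, keep baseline as the time origin but remove it from the times at which clearance can occur. Analyse time to viral clearance in patients with detectable PCR at baseline, and report the number excluded in each arm.
3. Apply the same condition to time to NS1 clearance, using detectable quantitative NS1 at baseline.

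The cost is a consistency amendment and a few sentences of analysis wording. No new samples are needed, because baseline viremia and quantitative NS1 are already collected. The one real drawback is that a few patients leave two secondary analyses, which departs from the stated intention-to-treat set. The criterion is measured before randomization, so the exclusion does not introduce selection by treatment.

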### Exclusion Criteria

1. Clinical signs and symptoms for severe dengue, such as:
   1. Severe abdominal pain
   2. Persistent vomiting
   3. Clinical fluid accumulation
   4. Mucosal bleed
   5. Altered mental state
   6. Liver enlargement > 2 cm
   7. Systolic blood pressure < 90 mm Hg
   8. Pulse pressure < 20 mm Hg
2. A person with any of the following laboratory values:
3. Hematocrit >52% males; >46% females
4. AST or ALT  1000 U/L
5. Room air oxygen saturation <95%
6. Absolute neutrophil count <1500 /µL
7. Platelet count <80,000/mm3
8. Creatinine >165 µmol/L males; > 130µmol/L females
9. Hemoglobin <13.0 g/dL males; <11.0 g/dL females
10. Total Bilirubin > 24 µmol/L
11. Serum creatine kinase > 600 U/L
12. History of or presently active intestinal disorders such as peptic ulcers, intestinal ulcers, intestinal obstructions, intestinal hernias, ulcerative colitis, malabsorption syndrome, celiac disease, Roemheld’s syndrome (gastroesophageal regurgitation disease) or Crohn’s disease
13. Severe diarrhea (grade 2 or higher according to NIH clinical trials guidelines)
14. Current usage of any anticoagulant drugs including, but not limited to, aspirin, warfarin, or clopidogrel
15. Any other clinically significant acute illness within 7 days prior to first study drug administration.
16. History of severe drug and/or food allergies.
17. Exposure to any new investigational agent within 30 days prior to the study drug administration.
18. Clinically significant abnormal physical examination unrelated to dengue infection, chest X-ray or 12-lead electrocardiogram (ECG) at screening, such as QTc prolongation (>450 msec).
19. Females of childbearing potential who are pregnant, breast feeding, or unwilling to avoid pregnancy by the use of appropriate contraception, including oral and subcutaneous implantable hormonal contraceptives, condoms, diaphragm, or intrauterine device (IUD), during the period that the experimental drug is administered. Prospective female participants of childbearing potential must have a negative pregnancy test (point of care)
20. Current significant medical condition or illness including cardiac arrhythmias, cardiomyopathy or other cardiac disease, asthma or other respiratory disease, diabetes mellitus, renal or hepatic impairment, thyroid disease, Parkinson’s disease, epilepsy or history of unexplained blackouts, immunocompromised state including known HIV infection, or any other illness that the Investigator considers should exclude the patient, especially those that require continuation of other medications likely to have an interaction with the study drug.
21. Any condition that would render the informed consent invalid, or limit the ability of the patient to comply with the study requirements.
22. Any condition that, in the opinion of the investigator, would complicate or compromise the study or well being of the patient.

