The human safety and tolerability of celgosivir has been tested in over 600 subjects at doses between 10 and 600 mg [Kaita 2007]. The drug has been chronically dosed with daily dosing for 12 weeks in over 340 HIV patients and 65 HCV patients. It also has been evaluated in some HCV patients for between 24 and 48 weeks at 400 mg PO daily [Durantel 2009]. Celgosivir is well absorbed with a Tmax <1 h and a half-life of 13-30 hr, with dose proportional exposure between 10 and 450 mg [Stoltz 1996, Sorbera 2005]. Celgosivir is rapidly converted to castanospermine, which is excreted unchanged in the urine, with no other metabolites detected. Adverse events were largely gastrointestinal, namely flatulence and diarrhea, of mild to moderate intensity. Asymptomatic elevations in serum creatine kinase were also observed, which were reversed within 2 weeks after discontinuation of the drug. No serious adverse events have been reported. Although celgosivir exhibited antiviral activity, it was not superior to existing treatments for HIV and HCV, and further development for those diseases was discontinued.

Celgosivir is in the class of alpha-glucosidase inhibitors. Another alpha-glucosidase I inhibitor, acarbose, is approved in the US, Europe and Singapore for treatment of Type 2 diabetes mellitus. The recommended dose of acarbose is 50 to 100 mg TID for a total daily dose of 150 to 300 mg.

In summary, the activity of celgosivir in several nonclinical *in vitro* dengue assays, reduction of viremia and significantly improved survival in animal models of dengue infection after celgosivir treatment, a record of safety and tolerability in human clinical trials for HIV and HCV up to 400 mg QD for 12 weeks, and the urgent need for dengue antiviral agent provide a compelling rationale for undertaking a proof-of-concept clinical trial of celgosivir for treatment of acute dengue fever.

Initiation of the trial will be contingent on obtaining approval of the relevant Investigational Review Board and the Health Sciences Authority of Singapore.

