## Dosing Regimen

Patients will be given an initial loading dose of 400 mg (4capsules). Subsequent dosing will be 200 mg (2 capsule) every 12 hr. The patient will receive a total of nine (9) doses, one 400 mg dose and eight (8) 200 mg doses. The capsule(s) should be administered with ~15 mL water. Drug should be taken 1 hr before consuming food or 2 hr afterwards.

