Upon admission, a clinical examination will be conducted, including ECG and chest X-ray. Blood samples will be taken for baseline assessments - viremia, quantitative NS1, IgG specific for previous dengue infection, hematology and coagulation, clinical chemistry, immunological profile, pre-dose pharmacokinetics, and DNA and RNA analysis. Urine will be collected for a pregnancy test (female patients only) and urine protein/ creatinine ratio and urinalysis (all patients). The patient will be asked to complete a visual analog scale for pain (VASP). The patient will then be randomized to placebo or celgosivir group. Capsules will be administered without food from Day 1 to Day 5. Patients will be placed on a special diet of protein, vitamins, and glucose containing minimal complex sugars or starches. Oral fluid intake, urine output, and stool frequency and consistency will be recorded, as well as any adverse events. Daily clinical exams will be conducted. Blood samples will be drawn daily while in hospital for hematology and clinical chemistry, viremia, quantitative NS1 levels, and immunological profiling (RNA expression levels and cytokines). Any subject who has a platelet count drop of ≥50,000/mm3 over a 24 hour period will require full blood count monitoring every 12 hr henceforth until platelet count trend reverses. Urinalysis will be conducted daily, and a sample of urine will be reserved for PK drug levels. Patients also will be asked to complete a VASP daily. Pain medications and any other concomitant medications will be recorded (date/time of ingestion and amount). Over the course of the hospital stay, eight blood samples will be obtained for pharmacokinetic assessments: one pre-dose sample will be taken on Study Day 1, three samples will be obtained on Study Days 2 through 4 between 1 to 3 hr after ingestion of drug (peak levels), and four samples will be obtained on Study Days 2 through 5 immediately prior to ingestion of the next dose (trough levels). The date and time of pharmacokinetic blood draws will be recorded on the CRF. On Study Day 5, after blood draws, administration of the last dose, safety assessments, determination of risk for DHF or DSS, and satisfactory clinical status, the patient will be discharged. Patients at risk for or who have dengue hemorrhagic fever (DHF) or dengue shock syndrome (DSS) will be transferred to a medical ward of the hospital until fit for discharge. Patients who progress to DHF or DSS may require intravenous fluids, platelet and/or blood transfusions and evaluations from other clinical specialists. They will be treated according to standard of care for DHF and DSS--primarily bed rest, fluids, as well as fever and pain medications (supportive therapy).

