## Criteria for Discontinuation of Patient Study Drug and for Study Termination

A patient’s study drug will be discontinued for

1) any patient developing severe dengue based on WHO criteria or

2) any patient developing grade 3 severity diarrhoea

The study will be terminated at any time that the Data Safety and Monitoring Board members conclude that:

1) Clear and significant harm is noticed in the treatment;

2) ≥30% serious adverse reactions occur in the treatment arm that are possibly, probably or definitely related to study drug;

3) ≥30% patients develop severe dengue based on WHO criteria;

4) ≥30% patients develop grade 3 severity diarrhoea;

5) The drop out rate is too high (>30%).

Figure 2 Flowchart of patients’ activities

Placebo

(N = 25)

Celgosivir

(N = 25)

Drug administration

Drug administration

Daily assessment

Daily assessment

Return to IMU for assessment

Return to IMU for assessment

Visit to polyclinic or GP/ED of NUH or SGH

Assessment of high probability of dengue infection

Fever ≥38° of ≤ 48 hr duration

≥2 symptoms of dengue fever

Positive NS1 strip assay

Others

Referral to IMU for screening of other inclusion & exclusion criteria

Written inform consent

Baseline assessment

Randomization

Discharge

End of Study

Day 5

Day 1

Day 1 to Day 5

Days 7, 10, 15

Day 15

Prior to Day 1

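### Exclusion 19 ends the contraception requirement at the last dose, although the protocol's own 13–30 hr half-life implies that 8–33% of drug-related exposure remains 48 hr later

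*Protocol*

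**What the plan says.** Exclusion 19 in Protocol section 3.2.2 bars women of childbearing potential who are pregnant, breast feeding, or unwilling to use one of the listed contraceptive methods "during the period that the experimental drug is administered". A negative point-of-care pregnancy test is needed at entry, and Table 2 schedules that test at screening only.

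The Dosing Regimen section sets the length of that period: "The patient will receive a total of nine (9) doses, one 400 mg dose and eight (8) 200 mg doses". Table 2 places the first dose at hour 0 and the last at hour 96, on Study Day 5. Patients are inpatients from Study Day 1 to 5. Section 5.1 puts the final dose among the steps completed before a patient is discharged on that day: "On Study Day 5, after blood draws, administration of the last dose, safety assessments, determination of risk for DHF or DSS, and satisfactory clinical status".

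On persistence, the Background states: "Celgosivir is well absorbed with a Tmax <1 h and a half-life of 13-30 hr". It adds: "Celgosivir is rapidly converted to castanospermine, which is excreted unchanged in the urine, with no other metabolites detected".

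Nothing in the protocol text available extends the contraception requirement beyond the last dose.

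**The concern.** The criterion does not leave the duration open. It names an end point, and that end point is the last dose. Because dosing and the inpatient stay cover the same days, the rule applies while the patient is in hospital and stops when she goes home, which is when pregnancy becomes a realistic possibility. By the protocol's own half-life, drug-related material is still present then.

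A woman who follows the criterion exactly may stop contraception straight after the last dose. In practice this concerns mainly users of condoms or a diaphragm, since an implant or IUD does not lapse on Day 5. The protocol's toxicology summary covers acute, repeat-dose, safety-pharmacology and genotoxicity studies and mentions no reproductive or developmental study. The document therefore offers no reason why exposure after the last dose can be disregarded. What is at stake is participant safety, not the validity of any comparison.

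**Working it through.** The protocol states no residual-drug or washout figure, so there is none to reproduce. The check asks what its half-life implies.

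**Inputs**
- Half-life: 13–30 hr (Background).
- Doses: 400 mg at hour 0, then eight doses of 200 mg every 12 hr, the last at hour 96 (Dosing Regimen; Table 2).
- Follow-up visits: Day 7 at 144 ± 24 hr, Day 10 at a nominal 216 hr, Day 15 at 336 ± 24 hr (Table 2).
- Assumptions: first-order elimination, and the quoted half-life describes drug-related exposure.

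**Share of the amount present at the last dose that remains t hours later:** 0.5^(t / half-life)

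| Time point | t after last dose | Half-life 13 hr | Half-life 30 hr |
|---|---|---|---|
| Day 7, earliest | 24 hr | 27.8% | 57.4% |
| Day 7, nominal (144 − 96) | 48 hr | 0.5^(48/13) = 7.7% | 0.5^(48/30) = 33.0% |
| Day 7, latest | 72 hr | 2.2% | 18.9% |
| Day 10, nominal (216 − 96) | 120 hr | 0.5^(120/13) = 0.2% | 0.5^(120/30) = 6.3% |

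**Washout of five half-lives (a convention, about 3% left).** 5 × 13 = 65 hr and 5 × 30 = 150 hr after the last dose. In study time that is 96 + 65 = 161 hr to 96 + 150 = 246 hr, i.e. Study Days 7 to 11. The required period ends at hour 96 and covers none of it.

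**Amount in the body.** These shares apply to an accumulated amount. Superposing the nine doses (one compartment, complete and instantaneous absorption assumed), the amount just after the last dose is 400 × 0.5^(96/h) + the sum over i = 1 to 8 of 200 × 0.5^((96 − 12i)/h), where h is the half-life.
- h = 13 hr: about 423 mg, falling to 423 × 0.077 ≈ 33 mg after 48 hr.
- h = 30 hr: about 780 mg, falling to 780 × 0.330 ≈ 257 mg after 48 hr. That exceeds one 200 mg maintenance dose.

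**Candidate end points at the 30 hr half-life**
- 7 days after the last dose: 168/30 = 5.6 half-lives; 0.5^5.6 = 2.1% left.
- Day 15, nominal: (336 − 96)/30 = 8.0 half-lives; 0.4% left.
- Day 15 window: 216/30 = 7.2 to 264/30 = 8.8 half-lives; 0.7% to 0.2% left.

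**The case against.** The strongest reply is that residual drug has been shown but harm has not. Genotoxicity tests were negative, the protocol reports no embryo-fetal signal and gives no exposure threshold, and the five-half-life convention comes from outside the document. All of this is correct. It limits the weight of the point, but it does not supply a reason for stopping at the last dose.

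Second, criterion 19 screens for willingness; it does not tell anyone to stop contraception. Instructions to participants may sit in the patient information sheet, which was not available for this review and may go further. If so, the eligibility criterion should still be brought into line with it.

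Third, the 48 hr point is a choice. It is the nominal Day 7 visit; across that visit's window the share runs from about 2% to 57%. The Background also does not say whether the half-life belongs to celgosivir or to castanospermine. Since conversion is rapid, the percentages are best read as drug-related exposure.

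Fourth, section 5.6 stops study drug for severe dengue or for "any patient developing grade 3 severity diarrhoea", which on the wording ends the required period sooner. Yet patients with or at risk of DHF or DSS stay in hospital until fit to leave, and those who cannot finish treatment are asked to complete all planned assessments. Early stoppers who follow the plan would therefore have more washout before going home than completers. The early-stop case carries weight mainly for patients who leave the study altogether.

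Finally, the reach is narrow: chiefly barrier-method users, for about 3 to 6 days by the washout convention, in a trial of 50 patients. That stands, and it is why the point is minor.

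**Conclusion.** The concern holds as a minor safety point. The contraception requirement ends at hour 96, on the day of discharge, while the half-life in the Background implies that 8–33% of the amount present at the last dose remains 48 hr later and up to about 6% at 120 hr. A washout of five half-lives would need a further 65–150 hr. The figures rest on first-order elimination, on the quoted half-life describing drug-related exposure, and on five half-lives as a conventional yardstick. They show persistence of drug, not a demonstrated risk to a fetus. Sample size, type I error, endpoints and analysis are not affected. The change is worth considering because it costs so little.

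**What to change.** Reword exclusion 19 so that contraception is required from the first dose until the Study Day 15 visit and, for patients who leave the study early, until at least 7 days after their last dose. State the same in the instructions given at Day 5 discharge, and check that the patient information sheet agrees.

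Seven days is the minimum that gives more than five half-lives at the upper end of the stated range. Day 15 goes beyond that, but it is an existing visit at which adherence can be confirmed. A single rule of 7 days after the last dose for everyone would also be defensible on these figures.

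The cost is one sentence in the criterion and one in the discharge instructions, with no added visit or test. A very small number of otherwise eligible women may decline because the commitment runs about 10 days longer, (336 − 96)/24 = 10.
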